**Table 1 Tab1:**
[figure not shown]
Schedule of enrolment, intervention and assessments

** Follow-up dates refer to date of initial fracture*

Process indicators relate to the medical and diagnostic guideline adherence of all participants and are derived from the documentation of FLS-CARE/study nurses as well as insurance claims data from the participating sickness funds. Additionally, contextual factors that facilitate or hinder the intervention and mechanisms of impact are identified through semi-structured interviews and questionnaires with relevant stakeholders in accordance with the Medical Research Council (MRC) guidance on process evaluation of complex interventions [15]. Parameters for the economic evaluation of the health care programme, next to the secondary fracture rate (effectiveness measure) and QALYs (utility measure), include implementation costs of FLS-CARE and overall treatment costs associated with the initial hip fracture from sickness fund data. Risk factors of secondary fractures and potential confounders of the treatment effect are collected using the Charlson Comorbidity Index (CCI), Elixhauser Comorbidity Index (ECI) and the fracture risk assessment tool of the IOF (FRAX®).

### Sample size

Sample size calculation is based on the comparison between the primary endpoint of the FLS-CARE group versus the control group in patients with femoral fragility fractures. Johansson et al. (2017) investigated the follow-up rate in severe osteoporotic fractures in a large study and found that the secondary fracture rate was 26% [16]. However, the exact follow-up period in which the secondary fractures occurred was unclear. In a study by Johnell et al. (2004) [17], a secondary fracture rate of 10% was observed in patients (mean age 80 years) with hip fractures 2 years after the initial fracture. Thus, this rate was assumed to approximate the value for the present control group. Following the method of Hemming et al. (2011) [18] for cluster-randomised studies with unequal cluster sizes, the number of cases per group for a given number of clusters can be determined as follows:
$$ {n}_C=\frac{n_ik\left[1-\rho \right]}{\left[k-{n}_i\left({cv}^2+1\right)\rho \right]}. $$where *n*_*i*_ corresponds to the individually randomised sample size, *k* to the number of clusters per group, *cv* to the coefficient of variation of a cluster and *ρ* to the intra-cluster correlation.

The participating hospitals are considered as cluster units. For the calculation of the number of patients needed for the analysis, 9 hospitals per group, an intra-cluster correlation of 1% and a coefficient of variation of clusters of 1.37 were assumed. Based on these values, 507 patients are needed per group to find a significant difference of 7% in the secondary fracture rate 2 years after the initial fracture (FLS-CARE group = 3% and control group = 10%) with a power of 80% and a significance level of 5%. The sample size was calculated using GPower 3.1 and R 3.3.2.

In the FAITH study (2014) [19], two surgical methods and their outcome after 2 years were studied in patients with fragility hip fractures. For sample size calculations, a mortality rate of 10% after 2 years and a lost to follow-up rate of 5% were taken into account. Owing to comparable patient populations regarding age and injuries, a similar drop-out rate is assumed for the FLS-CARE study. However, it is expected that the lost to follow-up rate will be 10%, especially in the control group. These considerations result in a total drop-out rate of 20% and a total number of 1216 patients (608 patients per group distributed over 9 clusters).

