### Recruitment

FLS-CARE or study nurses are responsible for recruitment to minimise selection bias. Once a patient is admitted to a participating hospital, the nurses are notified through the HIS or following a standardised communication protocol including the nurses and other hospital staff. If initial screening is positive, the attending physician will be informed about the potential study participant. Subsequently, information about either FLS-CARE or potential participation in a control group according to the study site is provided during the hospital stay. If the patient signs the informed consent, he or she, regardless of whether they are assigned to the control or FLS-CARE group, will be registered as a case in the FLS-CARE documentation module.

Duration of recruitment is limited to 12 months and is carried out under regular monitoring (weekly). In order to avoid a disproportionate distribution in one or more clinics, an upper limit of 104 patients per cluster is intended, which corresponds to an average recruitment frequency of two participants per week. Owing to the ongoing COVID-19 pandemic in 2020, the upper limit might be subject to minor adaptation if deemed necessary.

Consent is asked for further scientific use of the clinical data collected during hospital stay and follow-up phase (pseudonymised). Approval is sought to integrate close relatives or caretakers in the communication with the patient following legal regulations.

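### The sample size assumes a cluster-size coefficient of variation of 1.37, but at planned recruitment the cap of 104 patients per hospital allows at most about 0.71; the error is conservative, and the stated 80% power should be recalculated.

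*Protocol article*

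**What the plan says.** The Sample size section takes two-year secondary fracture rates of 3% (FLS-CARE) and 10% (control), 80% power, a 5% significance level and 9 hospitals per group. It applies a published formula for cluster trials with unequal cluster sizes, and states that "an intra-cluster correlation of 1% and a coefficient of variation of clusters of 1.37 were assumed". The result is that "507 patients are needed per group". After an allowance for 20% drop-out, the target becomes "608 patients per group distributed over 9 clusters", or 1216 in total.

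The Recruitment section then limits how uneven the hospitals may be: "an upper limit of 104 patients per cluster is intended". Its stated purpose is to prevent a lopsided distribution across clinics. Because of the pandemic, the limit may be changed, but only to a minor extent.

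Neither section gives a source for 1.37 or relates it to the cap.

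**The concern.** The two sections describe different trials. A cv of 1.37 with a mean of 67.6 patients per hospital implies a standard deviation of about 93 (1.37 × 67.6), while no hospital may exceed 104. The cv enters the formula squared, so it drives the result: 1 + cv² is 2.88 at 1.37 and about 1.51 at 0.71.

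If 1.37 cannot occur at planned recruitment, then 507 is not the number this design needs and 80% is not the power it has. That matters because the article itself expects recruitment delays and possible changes to the cap. Decisions on either would rest on a figure that does not describe the capped design, and the plan does not show how large an ICC or how small an effect the trial can absorb.

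**Working it through.** **Inputs (Sample size and Recruitment sections).** p₁ = 0.10, p₂ = 0.03, two-sided α = 0.05 (sidedness is not stated, but only a two-sided test reproduces the figure), power 80%, k = 9 hospitals per group, ρ = 0.01, cv = 1.37, N = 608 recruited per group, cap 104.

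**1. Reproducing 507.** The individually randomised size, with pooled variance under the null and p̄ = 0.065, is

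n_i = [1.96·√(2·0.065·0.935) + 0.8416·√(0.09 + 0.0291)]² / 0.07² = 193.5, rounded up to 194.

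The plan's formula, n_C = n_i·k·(1 − ρ) / [k − n_i·(cv² + 1)·ρ], then gives

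194·9·0.99 / (9 − 194·2.8769·0.01) = 1728.54 / 3.419 = 505.6, against the stated 507.

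Reading 1.37 as cv² + 1 gives about 273, so 1.37 was entered as the cv itself.

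**2. Largest cv under the cap at 608.** The mean is 608/9 = 67.56. The most uneven split is five hospitals at 104, one at 88 and three at 0.

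- Sum of squares: 5·104² + 88² = 61,824.
- Variance: 61,824/9 − 67.56² = 2,305.6, so the SD is 48.0.
- cv = 48.0/67.56 = **0.71** (0.75 with the n-1 SD).

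This lets three hospitals recruit nobody; requiring every hospital to recruit lowers the limit further.

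**3. What 1.37 would require.** The largest cluster is at least mean·(1 + cv²) = 67.56·2.8769 = 194 patients (180 with the n-1 SD), nearly twice the cap.

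**4. Does any lenient reading rescue 1.37?**

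- For a cap C and mean m, cv cannot exceed √(C/m − 1). With the cap raised to 125 this is √(125/67.56 − 1) = 0.92 (0.98 with n-1).
- Setting 507 analysed patients against the full cap (four at 104, one at 91, four at 0) gives 0.90 (0.95 with n-1).

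**5. Requirement at ICC 0.01, same formula.**

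| cv | denominator | n per group |
|---|---|---|
| 1.37 | 3.419 | 506 |
| 0.754 | 5.957 | 290 |
| 0.711 | 6.080 | 284 |
| 0.50 | 6.575 | 263 |

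**6. Power of the planned size.** Evaluable patients are 507 as stated, or 608 × 0.80 = 486 if 20% of the 608 drop out. The effective size is N / {1 + [(cv² + 1)·N/k − 1]·ρ}. For N = 486 and cv = 0.711:

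- Design effect: 1 + (1.505·54 − 1)·0.01 = 1.803, so the effective size is 269.6.
- Power: Φ{[0.07·√269.6 − 1.96·√0.12155] / √0.1191} = Φ(1.35) = **91%**.
- For N = 507 the result is 92% (91% at cv 0.754).
- With a t reference distribution on 16 degrees of freedom (18 hospitals minus 2), power at 486 is about 88%.

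**7. How far the margin stretches.** At 486 evaluable and cv 0.71, power is about 85% at ICC 0.015, 80% at about 0.019 and 67% at 0.03. ICCs above 0.01 are assumed here for illustration. At ICC 0.01, 80% power also holds for 10% versus about 3.9%. These figures use the normal approximation.

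**8. A recruitment shortfall.** The bound of 0.71 belongs to 608 recruited. Suppose 285 are evaluable, so 285/0.80 = 356 recruited. Under the same cap, 104, 104, 104, 44 and five at 0 is allowed. Then cv = 1.20 (1.27 with n-1), the formula requires about 405 (442), and power at 285 is about 73%.

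**The case against.** The strongest reply is that nothing is harmed. Too large a cv inflates the sample size, so the trial has more power than it claims, and the same 1216 patients would be recruited either way. This stands. It settles the direction of the error and makes this a correction of a planning figure, not a threat to the trial. It does not make 507 and 80% right for the capped design.

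A second reply is that 1.37 may come from uncapped hospital volumes, with the cap added as a safeguard. The article condenses a fuller protocol, so this cannot be excluded. It would explain the value but not reconcile it, because the calculation is presented for the trial that has the cap.

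A third reply is that the cap is only an intention, and that 1.37 becomes attainable if recruitment collapses. Under a cap of 104 that happens at about 325 per group (9·104/2.8769), or about 350 with the n-1 SD. This is correct, and it limits the point to planned recruitment. It does not help the plan, whose calculation leads to 608.

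A reader might also infer more than the documents support:

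- **That the target can be cut to about 285 per group, or that 285 is a safe floor.** Step 8 shows that the cv bound behind 285 fails once fewer patients are enrolled. The surplus also covers uncertainty in the ICC and in the effect.
- **That the cap should be dropped if 1.37 is truly expected.** The cap reduces the very imbalance that cv measures. At 486 evaluable and cv 1.37, power would be about 79% at ICC 0.01 and 68% at ICC 0.015.

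**Conclusion.** The concern holds in this limited form: at 608 patients per group over 9 hospitals, the assumed cv of 1.37 is incompatible with the intended cap of 104, which allows at most 0.71 (0.75 with the n-1 SD). A minor adaptation of the cap does not remove the conflict. At ICC 0.01, the stated 507 is about 1.7 to 1.8 times what the plan's formula requires at that limit (507/290 to 507/284).

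The error is conservative. The documents do not support a reading that the trial is underpowered on this account, nor one that the target should be reduced. The conclusion rests on full planned recruitment, the stated ICC and event rates, and equal retention across hospitals. The power figures of 91% to 92% use the normal approximation and are a few points lower with a small-cluster correction.

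**What to change.** - Replace 1.37 with a cv computed from the expected hospital volumes after applying the cap. Alternatively, give the source of 1.37 and explain how it fits with the cap.
- Keep the target of 1216 and the cap.
- Restate what 1216 delivers at the cap's limit: about 91% power at ICC 0.01 for 10% versus 3%, or about 80% power up to an ICC of about 0.019, or about 80% power for 10% versus about 3.9% at ICC 0.01. Show each with a 16-degree-of-freedom correction alongside.
- Add a short table of power across plausible values of cv and ICC.
- If a minimum evaluable number is stated for a recruitment shortfall, compute it with the cv expected at that lower recruitment (up to about 1.20 at 356 recruited per group). Do not give 285 as the floor.

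The cost is a recalculation and a few sentences of protocol text. No extra patients are needed, and the design and analysis do not change.

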**Methods:**

The study is set up as a non-blinded, cluster-randomised, controlled trial with unequal cluster sizes. Allocation to intervention group (FLS-CARE) and control group (usual care) follows an allocation ratio of 1:1 using trauma centres as the unit of allocation. Sample size calculations resulted in a total of 1216 patients (608 patients per group distributed over 9 clusters) needed for the analysis. After informed consent, all participants are assessed directly at discharge, after 3 months, 12 months and 24 months. The primary outcome measure of the study is the secondary fracture rate 24 months after initial hip fracture. Secondary outcomes include differences in the number of falls, mortality, quality-adjusted life years, activities of daily living and mobility.

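### The 20% drop-out allowance appears to have been added to 507 (× 1.2) rather than divided out (÷ 0.8), so 608 enrolled per group leave about 486 evaluable, not 507

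*Protocol article*

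**What the plan says.** The Sample size section introduces its inputs as those used to find the number of patients required for the analysis ("For the calculation of the number of patients needed for the analysis, 9 hospitals per group") and concludes that "507 patients are needed per group to find a significant difference of 7% in the secondary fracture rate 2 years after the initial fracture". So 507 per group is an analysable number, before any attrition.

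The next paragraph deals with attrition. It takes 10% mortality at two years from an earlier hip-fracture trial, raises that trial's 5% loss to follow-up to 10%, adds the two, and states "a total drop-out rate of 20% and a total number of 1216 patients (608 patients per group". The inflation formula is not printed.

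The Methods paragraph of the abstract gives the same total a different description: "1216 patients (608 patients per group distributed over 9 clusters) needed for the analysis".

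**The concern.** A drop-out rate is a proportion of those enrolled. The 10% mortality on which it is partly built can only be read that way. To keep a required number after losing a fraction *d*, one divides by 1 − *d*. Multiplying by 1 + *d* always gives too few. The three printed figures (507, 20%, 608) do not fit together under division but do fit under multiplication.

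If so, a trial that recruits exactly to target and loses exactly the planned proportion will still miss its own analysable number, and the stated 80% power is not the power at the expected number of evaluable patients. The abstract adds to the problem. A reader who takes its wording at face value would treat 1216 as the number to be analysed and expect enrolment to be larger still.

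**Working it through.** **Inputs (Sample size section).** Event rates 10% (control) and 3% (FLS-CARE); power 80%; significance level 5%; *k* = 9 hospitals per group; intra-cluster correlation ρ = 0.01; coefficient of variation *cv* = 1.37, so *cv*² + 1 = 2.8769; drop-out 10% + 10% = 20%. The article does not say whether the test is two-sided. I assume that it is, because this reproduces the plan's figure.

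**Step 1: reproduce 507.** A pooled two-proportion z-test without continuity correction needs *n*ᵢ = 194 per group under individual randomisation. The article's cluster formula then gives

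*n*_C = *n*ᵢ·*k*·(1 − ρ) / [*k* − *n*ᵢ(*cv*² + 1)ρ] = 194 × 9 × 0.99 / (9 − 194 × 0.028769) = 1728.54 / 3.419 = 505.6, i.e. 506.

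This agrees with the stated 507 to within rounding of the intermediate steps. A one-sided test would give 296. So 507 is confirmed as the number before attrition.

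**Step 2: find the route from 507 to 608.**

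| Route | Result per group |
|---|---|
| 507 × 1.20 | 608.4 (matches 608) |
| 507 / 0.80 | 633.75, i.e. 634 |
| 507 / (0.90 × 0.90), deaths and losses compounded | 626 |
| 507 / 0.85, with 5% loss to follow-up | 597 |
| 507 / (0.90 × 0.95), compounded with 5% loss | 593 |

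Only multiplication by 1.20 gives the printed number. The step is therefore inferred, but no other route tried comes out at 608.

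**Step 3: what 608 delivers.** 608 × 0.80 = 486.4 per group, or 972.8 in total, against 507 and 1014. The shortfall is about 21 per group and 41 in total. The drop-out that 608 can absorb while keeping 507 is 1 − 507/608 = 16.6%.

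**Step 4: effect on power.** Inverting the cluster formula gives the effective individually randomised size:

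*n*ᵢ = *n*·*k* / [*k*(1 − ρ) + *n*(*cv*² + 1)ρ]

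- At 507: 4563 / (8.91 + 14.586) = 194.2
- At 486.4: 4377.6 / (8.91 + 13.993) = 191.1
- At 608: 207.3

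Power is Φ{[0.07√*n*ᵢ − 1.96 × √(2 × 0.065 × 0.935)] / √(0.10 × 0.90 + 0.03 × 0.97)}. The two square-root terms are 0.3486 and 0.3451.

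- 507 evaluable: 80.1%
- 486 evaluable: 79.5%
- 608 evaluable (the abstract read literally): 82.6%

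**Step 5: the abstract.** The Sample size section attaches the description of patients needed for analysis to 507 per group (1014 in total). The abstract attaches it to 1216. Both cannot be right, and the derivation shows that 1216 is the number to enrol.

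**The case against.** The strongest objection is that nothing in the design turns on this. Power of 80.1% and 79.5% both print as 80% to the whole per cent. Raising the assumed intra-cluster correlation from 0.010 to 0.011 would cost about 2.4 points (80.1% to 77.7%), roughly four times as much. This stands: it bears on how much weight the point deserves, but it does not make the figures agree.

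Second, the Recruitment section intends a cap of 104 patients per hospital. If 608 are enrolled per group (mean 67.6 per hospital) and the cap holds, the cv cannot exceed roughly 0.73 to 0.78, far below 1.37. On such values the same formula would ask for only about 287 to 294 patients per group, and 486 would give about 90 to 91% power. This is a separate question about the cv assumption and does not reconcile 507, 20% and 608. It is, however, a good reason not to raise the recruitment target because of this error.

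Third, the Statistical methods and Additional analyses sections plan intention-to-treat analysis, mixed models and multiple imputation, and the Data collection section allows parameters to be collected by telephone. Patients who leave early may therefore still contribute. But imputation is planned only where possible, and the sample size calculation itself treats the 20% as lost; otherwise no allowance would be needed.

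Fourth, the higher loss to follow-up is expected mainly in the control group. If the intervention group lost only 5% to follow-up (15% in all), 608 × 0.85 = 517 would remain there. The control group would still have 486, and the article applies 20% to both groups.

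**Conclusion.** The concern holds. With the article's own 507 and 20%, an enrolment of 608 per group leaves about 486 evaluable, a shortfall of about 21 per group. Compounding the two sources of loss (0.81 retained) leaves about 492, still short. The description in the abstract contradicts the Sample size section.

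The consequence is small: about 0.6 percentage points of power. That rests on the plan's stated event rates, intra-cluster correlation, cv and nine hospitals per group, a two-sided 5% test, and drop-outs contributing nothing. Multiplication by 1.2 is an inference, since the article does not print the step, but the mismatch between 507, 20% and 608 does not depend on it. It should be corrected because it affects the trial's headline sample size and costs almost nothing to put right.

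**What to change.** 1. In the Sample size section, keep 608 per group (1216 in total) as the enrolment target. State that 20% drop-out leaves about 486 evaluable per group (973 in total), and give the power at that number (about 79.5% on the stated inputs). Print the inflation step so that it can be followed.
2. In the abstract, describe 1216 as the number to be enrolled, not the number needed for the analysis.
3. Make the same correction wherever else the figure is repeated with either meaning.

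Holding strictly to 507 evaluable would need 634 per group (1268 in total, 52 more than planned). Given how little power this buys, I would not recommend it on this ground alone.

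The cost is wording and one restated figure, with no additional patients and no change of design.

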### Recruitment

FLS-CARE or study nurses are responsible for recruitment to minimise selection bias. Once a patient is admitted to a participating hospital, the nurses are notified through the HIS or following a standardised communication protocol including the nurses and other hospital staff. If initial screening is positive, the attending physician will be informed about the potential study participant. Subsequently, information about either FLS-CARE or potential participation in a control group according to the study site is provided during the hospital stay. If the patient signs the informed consent, he or she, regardless of whether they are assigned to the control or FLS-CARE group, will be registered as a case in the FLS-CARE documentation module.

Duration of recruitment is limited to 12 months and is carried out under regular monitoring (weekly). In order to avoid a disproportionate distribution in one or more clinics, an upper limit of 104 patients per cluster is intended, which corresponds to an average recruitment frequency of two participants per week. Owing to the ongoing COVID-19 pandemic in 2020, the upper limit might be subject to minor adaptation if deemed necessary.

Consent is asked for further scientific use of the clinical data collected during hospital stay and follow-up phase (pseudonymised). Approval is sought to integrate close relatives or caretakers in the communication with the patient following legal regulations.

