## Methods

### Trial design

The study is set up as a non-blinded, cluster-randomised, controlled trial with unequal cluster sizes. Allocation to intervention group (FLS-CARE) and control group (usual care) follows an allocation ratio of 1:1 using hospitals (trauma centres) as the unit of allocation. In total, 18 study sites (9 hospitals per group) across Bavaria participated in the study. The cluster-randomised study design was chosen to avoid contamination bias by clinical staff and other patients within one centre.

For the purpose of this study, only trauma centres located in one federal state of Germany (Bavaria) are included.

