#### Identification of eligible patients

Depending on the study arm, either FLS-CARE or study nurses identify potential patients using pre-agreed protocols through the hospital information system (HIS). If the screening of eligible patients is successful, the nurse informs the attending physician who is responsible for obtaining informed consent. After receiving details of study participation, every patient has at least 24 h for consideration. Once enrolled in the study, the participant can withdraw within 2 weeks through their sickness funds without giving reasons and thereafter through a declaration of will [10]. Clear guidelines on the withdrawal process are provided for all participants at the time of enrolment.

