### Allocation

The allocation ratio of participating hospitals is set to 1:1 with unequal cluster sizes. In order to achieve similar clusters between the FLS-CARE and control groups, the hospitals are stratified by type (local/regional and superregional trauma centre) and location according to a simplified classification (metropolis yes/no). To eliminate selection bias, the trust centre of the evaluating institution of the study (LMU-HSM) was included in the sequence generation process to pseudonymise (conceal) all potential trauma centres before randomisation into FLS-CARE and control groups. The randomisation was performed by LMU-HSM using R 3.3.2.

Owing to the nature of the study, blinding of neither the study participants nor the FLS-CARE/study nurses is feasible.

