### Trial status

The present paper is the first version of the study protocol dated 26/10/2020. At the time of writing, the study is in the preparatory phase. Recruitment, which was originally planned to start in July 2020 and to be completed after 1 year, has been postponed until November 2020.

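### Patients are screened, informed and consented after their hospital's arm is fixed, by unblinded arm-specific staff, so nurse-led recruitment does not support the claim of minimising selection bias

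*Protocol article*

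**What the plan says.** **Order of events.** Under Trial design, allocation "follows an allocation ratio of 1:1 using hospitals (trauma centres) as the unit of allocation". The Allocation section reports the randomisation as already done: "The randomisation was performed by LMU-HSM using R 3.3.2". Trial status describes the study as preparatory and says that recruitment "has been postponed until November 2020".

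**Who finds and consents patients.** The section on identifying patients has arm-specific staff do the screening: "Depending on the study arm, either FLS-CARE or study nurses identify potential patients using pre-agreed protocols", working through the hospital's information system. The same section makes the attending physician responsible for consent.

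**What patients are told.** Under Recruitment, "information about either FLS-CARE or potential participation in a control group according to the study site is provided during the hospital stay". Only those who sign are registered as cases.

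**Blinding and concealment.** Under Allocation: "Owing to the nature of the study, blinding of neither the study participants nor the FLS-CARE/study nurses is feasible". The concealment step in that section pseudonymises trauma centres before they are randomised.

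**The stated patient-level safeguard.** "FLS-CARE or study nurses are responsible for recruitment to minimise selection bias".

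**Other measures that bear on the point.** These are the pre-agreed screening protocols, a standardised communication protocol, weekly recruitment monitoring, and collection of FRAX and the Charlson and Elixhauser indices. Statistical methods accepts that stratification cannot guarantee comparable groups and leaves the need for adjustment to be examined when the analyses begin.

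**The concern.** In a cluster trial, randomising hospitals balances hospitals. It balances patients only if their entry into the trial does not depend on the allocation. Here entry can depend on it in two ways. The person who screens knows the arm and, in FLS-CARE hospitals, is also the person who will coordinate the programme. The offer put to the patient differs too: one site offers a programme with home visits, telephone calls and coordinated therapy, the other usual care with scheduled data collection. Willingness to accept these two offers may be related to frailty, motivation and likely adherence, and so to fracture, falls and death.

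At stake is the primary comparison. Intention to treat starts from the patients who consented, so it preserves an imbalance in who consented. Adjustment corrects only for what is measured. More patients do not shrink a bias of this kind, and it cannot be fully repaired later if nothing is recorded on those who were not approached or who declined.

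**Working it through.** **Step 1: sequence.** Set side by side, Trial design (hospitals are allocated), Allocation (randomisation in the past tense) and Trial status (recruitment still to come) show that every patient is identified after the hospital's arm is fixed.

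**Step 2: knowledge of the arm.** The type of nurse depends on the arm, and Allocation states that the nurses are not blinded. That the consenting physician knows the arm is not stated outright. It follows from hospital-level allocation and site-specific patient information.

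**Step 3: does the safeguard reach the risk?** Pre-agreed screening through the information system acts on which patients come to the nurse's attention. It does not act on what the patient is offered or on who accepts. Pseudonymising centres acts on the allocation of hospitals. Neither covers arm-dependent consent.

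**Step 4: reproduce the plan's sample size, to have a scale.** Inputs from the Sample size section: 10% and 3% at two years, 80% power, 5% significance (taken as two-sided), k = 9 hospitals per group, ρ = 0.01, cv = 1.37.

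- Individually randomised size, pooled-variance formula without continuity correction: n_i = [1.96·√(2·0.065·0.935) + 0.842·√(0.10·0.90 + 0.03·0.97)]² / 0.07² = 193.5, rounded up to 194.
- Plan's cluster formula: n_C = n_i·k·(1−ρ) / [k − n_i·(cv²+1)·ρ] = 194·9·0.99 / (9 − 194·2.8769·0.01) = 1728.5 / 3.419 = 505.6, so 506 against the stated 507.
- Design effect at 507 per group: 1 + (2.8769·507/9 − 1)·0.01 = 2.61. Effective size: 507 / 2.61 ≈ 194 per group.

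**Step 5: illustration with no treatment effect.** The risk strata and mixes are assumptions; the documents give none. Take eligible patients as half at 6% risk and half at 14%, mean 10%, with the control arm recruiting that 50:50 mix.

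- 60% lower-risk in FLS-CARE: 0.6·6% + 0.4·14% = 9.2%; difference 0.8 points, which is 0.8/7 = 11% of the planned effect.
- 70% lower-risk: 0.7·6% + 0.3·14% = 8.4%; difference 1.6 points, which is 1.6/7 = 23%.

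The chance that an unadjusted test falsely favours FLS-CARE is Φ[(d − 1.96·SE₀)/SE₁], where d is the risk difference, SE₀ the pooled and SE₁ the unpooled standard error at effective n = 194 per group. The nominal value in that direction is 2.5%.

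| Risk in FLS-CARE arm with no effect (control 10%) | Chance of false benefit |
|---|---|
| 9.2% | 4.5% |
| 9% | 5% |
| 8.4% | 8% |
| 8% | 10% |
| 7% | 18% |
| 6% | 31% |

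An imbalance the other way would hide a real benefit instead.

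**Step 6: cost of a two-stage consent that keeps decliners.** Assume that a share q of FLS-CARE patients declines the programme and carries control risk. The arm's rate becomes 3%·(1−q) + 10%·q. Power is computed at the same effective size; required n per group uses the plan's own formula.

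| q | FLS-CARE rate | Power at 507 | n per group for 80% |
|---|---|---|---|
| 0% | 3.00% | 80% | 506 |
| 5% | 3.35% | 75% | 734 |
| 10% | 3.70% | 69% | 1283 |

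Even 5% refusal asks for more evaluable patients than the 608 per group to be enrolled. With nine hospitals per group the formula is steep, so such dilution is not slight.

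**The case against.** Much can be said for the plan. It says *minimise*, not *remove*, and dedicated nurses working from an information-system screen may well find cases more evenly than busy clinicians would. The word *eliminate* in Allocation refers to the concealment of hospitals and makes no claim about patients. FRAX, a dedicated fracture-risk tool, is collected along with two comorbidity indices, and adjusted models are foreseen. Recruitment after allocation is common in cluster trials of care programmes that cannot be blinded, and the article discloses the lack of blinding and justifies the design by contamination.

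All of this stands as mitigation. None of it makes consent independent of the arm, and adjustment that depends on a look at baseline balance is weaker than adjustment fixed beforehand.

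A reader might infer more than the documents support:

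- *That the immobility exclusion is applied without a threshold.* The pre-agreed protocols are not shown, so this cannot be asserted.
- *That the cap of 104 lets busy sites choose patients.* The cap is a total per hospital. The planned mean is 1216/18 ≈ 68, and no admission figures show that any site would have a surplus.
- *That no screening log exists.* The flowchart and the full protocol are not shown.
- *That the arms will differ by 0.8 to 1.6 points.* Those figures come from assumed strata, and the direction could reverse.

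**Conclusion.** The concern holds in a limited form. The documented procedure leaves identification and consent open to influence by the arm, so the statement that nurse-led recruitment serves to minimise selection bias is not supported by the procedure it describes. Concealment protects the allocation of hospitals and nothing beyond it. The plan's baseline risk data reduce the exposure without closing it.

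The documents do not show that the arms will differ, or by how much. Step 5 gives scale only: modest shifts in recruited risk would raise the chance of a false benefit from 2.5% to between about 4.5% and 10% for FLS-CARE risks of 9.2% to 8%. This assumes no treatment effect, an unadjusted test, and the plan's intra-cluster correlation and coefficient of variation. The conclusion also rests on the inference that the consenting physician knows the arm.

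**What to change.** 1. Approach all eligible patients listed by the information system consecutively in both arms, under one screening protocol and one set of eligibility definitions.
2. Keep a log of listed, eligible, approached and consenting patients, with age, sex, fracture type and reason for non-inclusion. Compare it by arm in the weekly monitoring and in the final report.
3. Word the general study information and the data-collection consent identically and neutrally in all 18 hospitals.
4. Fix in advance the adjustment of the primary model for baseline risk factors already collected, for example age, sex, FRAX and the Charlson index, instead of deciding after a look at balance.
5. Restate Recruitment and Allocation to say that concealment covers hospitals only and that patient-level recruitment bias remains possible.

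**Cost.** Items 1 and 2 build on the screening and monitoring already planned, with a short log added. Item 3 needs an amendment to the consent documents. The article is dated 26/10/2020 and recruitment was due in November 2020, so time was short, but no patient had yet been recruited. Items 4 and 5 are changes of text.

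A common first-stage consent that keeps programme decliners in the analysis would deal more directly with arm-dependent consent. It is an option to weigh and not a required change: under the Step 6 assumptions power falls to about 75% at 5% refusal and 69% at 10%, and staff would still know the arm when approaching patients.
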